## Abstract

**Background:**

Traumatic exposure is a frequent issue in patients visiting emergency departments (EDs). Some patients will subsequently develop post-traumatic stress disorder (PTSD) while other will not. The problem is under-diagnosed in EDs and no standardized management is provided to prevent PTSD. Most studies focused on a particular group of trauma whereas we need a global approach to further develop interventions for detecting and treating patients at high risk. We aim to assess the prevalence of traumatic exposure and situation at high risk of further PTSD and identify pre and peri-traumatic biopsychosocial factors predisposing individuals to PTSD in the general context of EDs.

**Methods:**

This comprehensive multicenter study will have two steps. The first step will be a cross-sectional study on moderate and high risk of PTSD prevalence among EDs visitors with a recent history of trauma. All patients aged 18–70 years, presenting with a recent history of trauma (< 1 month) in one of the six EDs in the Auvergne-Rhône-Alpes region (≈1/10° of the French population) will be included over a 1-month period and approximately 1500 subjects are expected in this cross-sectional step. The risk of PTSD will be assessed using the Impact of Event Scale Revised (IES-R). Self-administered questionnaires will be used to measure acute stress (IES–R), and a number of potential bio-psycho-social risk factors. Demographic and physical health-related data will be collected from medical file. Second step will be a prospective cohort study within a sub-sample of 400 patients enrolled in step 1, randomly selected with stratification on sex, age, ED, and IES–R score. At 3 months, PTSD will be defined by a ≥ 33 score at PTSD Check List for DSM–5 (PCL–5) through a telephone interview. We will evaluate definite PTSD biopsychosocial predictive factors using a multivariate logistic regression model and describe evolution of PTSD at 3 months.

**Discussion:**

This is the first study to assess PTSD predictors prospectively with a biopsychosocial approach within a cohort representative of EDs visitors. The results will inform the development of dedicated interventions to decrease the risk of subsequent PTSD.

**Trial registration:**

ClinicalTrials.gov: NCT03615014; ISSUE protocol 2nd version was approved on 07/08/2018.

## Background

Post-traumatic stress disorder (PTSD), one of the most serious sequelae of a traumatic exposure, is a chronic disorder with a high level of anxiety and neurovegetative symptoms that interrupt normal psychosocial functioning of the person [1–4]. There are four main categories of diagnostic symptoms, namely, symptoms of re-experiencing the trauma, avoidance and numbing symptoms, negative alterations in mood and cognition, and hyper-arousal symptoms. [4–9]. The mean duration of PTSD is 5.3 years (range: 0.2–28.1) [10]. Patients with PTSD are more likely to develop other psychiatric disorders such as depression, anxiety disorders, substance use disorders, and/or attempt suicide [11, 12]. The likelihood of developing somatic pathologies such as cardio-vascular disorders is also very high [13, 14]. Therefore, such patients, in addition to the disorder itself, suffer from its physical, occupational, and social sequelae. Such consequences result in a significant economic impact [5].

Worldwide approximately 60.7% of all men and 51.2% of all women encounter at least one traumatic event in their lifetime. However, not all of them will develop PTSD; it is estimated that after a trauma, 8% of men and 20% of women will subsequently develop PTSD [15]. Prevalence of the condition is highly variable (4–86%), but is higher among those who experienced the stressors directly, such as victims of intimate partner violence (IPV), sexual victimization, servicemen, refugees, and asylum seekers [5]. In the French population, the lifetime exposure to a traumatic event is estimated to be 72.7% and lifetime prevalence of PTSD to 3.9% [10], which is lower than that found in the United States (7.8%), but higher than rates in Spain (2.2%) or Italy (2.4%) [10].

Among the patients consulting EDs after a recent trauma, 18 to 42% suffer from acute stress disorder (ASD) [16–18], which is highly predictive of subsequent occurrence of PTSD [16, 19, 20]. However, ASD is often underdiagnosed in ED, mainly due to the assessment focused on urgent physical problems, complaints of the patient (pain, insomnia), and overlooking the traumatic context [1, 21].

PTSD predictive factors are worthwhile for identifying populations at high risk, which in turn could lead to early diagnosis and management of these cases, and therefore could help reduce the occurrence of the disorder. Screening for such factors, however, is not incorporated into any structured assessment procedure in EDs.

Previous research has identified the following predictive factors for PTSD: pre-traumatic factors (e.g. female sex, extreme age, low Intelligence quotient (IQ), childhood or prior traumatic exposure, pre-existing mental health problem, substance abuse, anxious personality), specific features of the index trauma (perception of death threat, head trauma, intentional aggression), and post-traumatic psychosocial factors such as peri-traumatic dissociation, acute stress disorder and low social support [1–3, 5, 15, 21–40]. However, these studies have methodological limitations. For instance, they suffer from selection bias as they usually focus only on a particular population [32, 41–44] or on a single trauma type such as road traffic accident [32, 43–46]. Most used case-control or retrospective designs that suffer from information/recall bias [41, 42, 44, 46–49], and were conducted on small samples and/or had high loss-to-follow-up rates for prospective studies reducing the generalization of the results [20, 26, 28, 43, 45, 46, 50–54]. Furthermore, studies usually focused on either biological, psychological, or social factors; none considered a comprehensive biopsychosocial approach to study the predictive factors [19, 20, 25, 32, 48, 50, 52, 54, 55]. It is also of note that, to the best of our knowledge, there is no published prospective epidemiological study that has evaluated the prevalence of acute stress in survivors of diverse trauma visiting an ED.

We therefore aim to address all these limitations in a prospective multicenter study that will recruit a large number of patients in the ED who were exposed to various types of trauma. We will measure prevalence of acute stress and level of PTSD risk through an initial cross-sectional study. We will then adopt a holistic viewpoint to determine the predictive factors such as specific features of the trauma as well as demographic, biological, psychological and social risk factors through a cohort study.

## Objectives

### Primary objectives

The primary objective of the cross-sectional study is to estimate the prevalence of patients with high or moderate risk of developing PTSD in all consecutive cases admitted to the EDs after recent trauma (< 1 month).

The primary objective of the prospective cohort study is to determine predictors of PTSD occurrence at 3 months in a randomly selected sub-sample of patients included in the cross-sectional study and identified as “at moderate or high risk” for developing PTSD at admission to the ED.

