## Methods/design

This multicenter study will be conducted in two stages. The first stage will consist of a cross-sectional study within all consecutive patients admitted to the participating EDs following a recent trauma (< 1 month), to systematically measure their risk of PTSD. The second stage will be a prospective cohort study designed to analyze the relationship between PTSD occurrence and its putative predictive factors in a sub-sample of patients randomly selected among those identified as “at moderate or high risk” for developing PTSD at admission to the ED and followed-up for 3 months.

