### Constitution of the cohort

The prospective cohort study will be conducted on a sub-sample of the participants (Fig. 1). The study biostatistician will arrange a cohort of 400 subjects selected through random sampling stratified by sex (male/female), age (determined by interquartile range of the collected data), investigating ED (1 to 6), and IES-R score (< 12, 12 to 34, > 34). Selected subjects will receive the questionnaires by email or postal mail and will be interviewed by telephone at 3 months (± 15 days) after the index trauma. Mental health professionals (a psychologist, psychiatrist, or resident in psychiatry) who have had special training on the PCL–5 application will conduct the interview.

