### Outcome criteria and measure instruments

#### Primary outcome criteria

The primary endpoint for the cross-sectional study is the IES–R score of the subjects reflecting their risk of developing PTSD at inclusion in the ED. An IES-R score > 34 will be considered as a high-risk of subsequent PTSD, an IES-R score of 12–34 as a moderate risk, and an IES-R <  12 a low risk [44, 56, 57]. IES-R is a 22-item self-administered questionnaire composed of three subcomponents: intrusion (8 items), hyperarousal (6 items), and avoidance (8 items). Patients evaluate for each item the experience during the last 7 days on a Likert scale 0 = not at all to 5 = extremely. The total score (from 0 to 88) is the sum of all the evaluations. IES-R has good psychometric characteristics [56–62], and is recommended in France for PTSD surveillance [63]. The IES-R is among the most used scales [64], it is validated in French with a mean completion time of 5 to 10 min [65].

The primary endpoint of the prospective cohort study is the presence or absence of 3-month PTSD defined by PCL-5 (PTSD Check List for DSM-5). PCL-5 is a 20-item self-reported measure. Consistent with the Diagnostic and Statistical Manual of Mental Disorders, Fifth Edition (DSM-5), it assesses 20 symptoms of PTSD. The questionnaire uses “0=not at all” to “4 = extremely” ratings to evaluate each symptom. A probable diagnosis of PTSD is made by considering any item with a score of ≥2 as present and then by adhering to DSM-5 instructions that require at least: 1 item B (questions 1–5), 1 item C (questions 6(− 7), 2 items D (questions 8–14), and 2 items E (questions 15–20). The cut-off score for PCL-5 is ≥33 [66, 67]. This tool has a good sensitivity for a provisional diagnosis of PTSD, and has the advantage to have a shorter completion time (about 5 to 10 min) than the CAPS–IV [16, 19, 20].

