##### Among subjects with 3-month PTSD

To describe PTSD complications and comorbidities, we will consider the proportion of patients with excessive alcohol consumption (AUDIT), the proportion of patients with tobacco addiction and its level (low, medium or high; Fagerström test), the severity of depressive symptoms (QIDS) and the proportion of patients in each of the five categories (from no depression to very severe depression), and the response to item 12 of QIDS-SR16 which will depict proportion of subjects with suicidal ideation.

We will use mean, standard deviation, median, and interquartile range to illustrate the number of days lost from work and the number of suicide attempts over the last 3 months. The proportion of patients with at least one of these events will also be measured.

We will present secondary endpoint results for the total study population and the subgroups according to the level of risk identified at inclusion by the IES–R score (moderate risk = IES-R score 12 to 34; high risk = IES-R score > 34).

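### The cohort objective is limited to moderate- or high-risk patients, but the sampling plan also draws a low-risk stratum, and the 40% incidence assumption is tied to neither population

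*Protocol article*

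**What the plan says.** Two sections restrict the cohort by risk level. Primary objectives places the search for predictors in patients "identified as “at moderate or high risk” for developing PTSD at admission to the ED". Methods/design repeats this and describes "a sub-sample of patients randomly selected among those identified as “at moderate or high risk” for developing PTSD at admission to the ED".

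Primary outcome criteria fixes the meaning of the levels: a score above 34 is high risk, with "an IES-R score of 12–34 as a moderate risk, and an IES-R < 12 a low risk". The restricted cohort therefore has IES-R of 12 or more.

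Constitution of the cohort is the working instruction to the biostatistician. It draws the 400 by random sampling stratified on sex, age, "investigating ED (1 to 6), and IES-R score (< 12, 12 to 34, > 34". The lowest of these three score bands is the low-risk group. The Discussion paragraph of the Abstract speaks of predictors assessed "within a cohort representative of EDs visitors", without limiting this to a risk level. Table 1 calls the stratified sampling weighted and gives no weights.

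Sample size assumes 40% incidence in the unexposed and a relative risk of 1.4. It asks for 305 patients at alpha 0.05 and 80% power, and selects 400 to allow for losses. The 40% comes from a 30% to 60% range over various populations and trauma types. Under Statistical methods, the primary analysis expects 122 PTSD cases among the 305 and caps the multivariate model at twelve variables on that basis.

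**The concern.** A cohort restricted to IES-R of 12 or more cannot contain a stratum below 12. If the draw follows the sampling section, some of the 400 places go to patients outside the primary objective, and the analyst then has two courses. Dropping them to honour the objective shrinks the sample on which the power rests. Keeping them means that the 3-month incidence and the associations describe a wider population than the one stated.

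The incidence assumption does not settle the matter, because it is not attached to any IES-R level. It cannot be right for both populations unless low-risk patients develop PTSD as often as the others, and then the risk classification would carry no information.

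**Working it through.** **Inputs from the article.** Unexposed incidence 40%, relative risk 1.4 (so 56% in the exposed), alpha 0.05, power 80%, 305 analysable patients, 122 expected events (40% × 305), twelve variables.

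**Inputs assumed.** Two-sided test and 1:1 exposure, which are not stated but reproduce the plan's number. Low-risk share w of the analysable sample, 10% to 50%. Low-risk incidence q, 5% to 10%. The article gives no figure for w or q.

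**Reproducing the plan's figure.** Per group, with p̄ = 0.48 and d = 0.16:

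n = [1.960 × √(2 × 0.48 × 0.52) + 0.842 × √(0.40 × 0.60 + 0.56 × 0.44)]² / 0.16² = (1.385 + 0.587)² / 0.0256 ≈ 152.

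That is 304 in total, against 305 stated. Power at 305 is 80.2%. The arithmetic is sound on its own inputs.

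**Course A: low-risk patients drawn, analysis restricted to IES-R 12 or more.** The sample is 305 × (1 − w), and power is for 40% vs 56% at that size.

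**Course B: low-risk patients kept.** The unexposed incidence becomes p₀ = 0.40 × (1 − w) + q × w, and power is for p₀ vs 1.4 × p₀ at 305. For example, with w = 50% and q = 5%, p₀ = 0.20 + 0.025 = 22.5%; the comparison is 22.5% vs 31.5% and power is 42%. Events follow the plan's own convention, p₀ × 305.

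| Low-risk share | A: patients left | A: power | B: unexposed incidence | B: power at 305 | B: events |
|---|---|---|---|---|---|
| 10% | 274 | 76% | 36.5–37.0% | 73–74% | 111–113 |
| 20% | 244 | 71% | 33.0–34.0% | 66–68% | 101–104 |
| One third | 203 | 63% | 28.3–30.0% | 55–59% | 86–92 |
| 50% | 152 | 51% | 22.5–25.0% | 42–48% | 69–76 |

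**Variable limit.** The plan has 122 / 12 ≈ 10 events per variable. Under course B this becomes 113 / 12 ≈ 9 at best and 69 / 12 ≈ 6 at worst.

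**Why 305 is the base.** Selecting 400 and losing 30% leaves 400 × 0.7 = 280, where power is 76.7% with no low-risk patient at all. That shortfall is a separate matter. Starting from 280 would charge it to the population conflict.

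**The case against.** The strongest reply is that the conflict is narrow and its consequences unknown. Much of this stands.

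- A reader might infer that the Methods paragraph of the Abstract also contradicts the objective. It does not: "a sub-sample of 400 patients enrolled in step 1, randomly selected with stratification on sex, age, ED, and IES–R score" does not say that every risk level is eligible. Moderate- and high-risk patients are all enrolled in step 1, and stratifying on the score works with two bands as well as three.
- A reader might take the subgroup text, "moderate risk = IES-R score 12 to 34; high risk = IES-R score > 34", as proof that only these levels enter the cohort. It is not: the same sentence also promises results for the total study population, and it covers secondary endpoints in general.
- A reader might say that the incidence assumption and the power refer to different populations. They share one 40% figure. What can be said is that this figure is tied to neither cohort definition.
- The representativeness phrase in the Abstract is a general claim, perhaps meant as a contrast with single-trauma studies. It is weak evidence about the sampling frame, though it still needs to match the population chosen.
- The weighting in Table 1 could make the low-risk share small, and Fig. 1, which may show how the cohort is formed, is not available here. A large loss of power is therefore possible but not shown.

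None of this removes the core conflict. The objective and design sections restrict the cohort, the sampling section names a stratum that the restriction rules out, and no text at hand reconciles them.

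**Conclusion.** The point holds as a contradiction between Primary objectives and Methods/design on one side and Constitution of the cohort on the other, together with a 40% incidence anchored to neither. That part rests on the text alone and is firm.

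Its size is conditional. With a low-risk share of 10% to 50%, power at the planned 305 falls from 80.2% to about 76% to 51% if the analysis is restricted. If low-risk patients are kept at 5% to 10% incidence, it falls to about 74% to 42%, with expected events of about 113 to 69 instead of 122. These figures also assume 1:1 exposure, a two-sided test, 40% unexposed incidence in patients scoring 12 or more, and, where low-risk patients are kept, a relative risk of 1.4 in the mixed cohort. If the cohort is drawn only from IES-R of 12 or more, the 305 stands, provided that 40% is right for that group. The documents do not show which population the sponsor intended.

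**What to change.** Before the draw, make Primary objectives, Methods/design, Constitution of the cohort and the Abstract's Discussion paragraph name one population, and state that the 40% refers to it. There are two ways:

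1. **Keep the objective.** Remove the stratum below 12 and draw all 400 from the 12–34 and above-34 strata, after checking that enough such patients have been enrolled; the article gives no IES-R distribution from which to tell. Limit the representativeness claim to ED trauma patients at moderate or high risk. The cost is wording, one change to the sampling program and that check.
2. **Keep the three strata.** Widen the objective to all risk levels, state the sampling fraction in each stratum and weight the incidence estimate accordingly. Restate the assumed incidence, expected events, variable limit and power for that population at the planned 400, without enrolling more. The cost is wording, a revised calculation and an open statement of lower power.

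The choice belongs to the sponsor. It has to be made before selection, because places given to low-risk patients may not be recoverable afterwards.

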### Secondary objectives

The secondary objectives are to measure acute stress, anxiety disorder, and dissociative experiences in patients at inclusion. At 3 months, the incidence of PTSD, its complications and comorbidities will be estimated, as well as the impact of trauma on occupational and psychosocial functioning of the study subjects.

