### Participant eligibility

The target population will be adults (≤ 70 years of age) visiting the EDs during the 1-month inclusion period who were victims of a recent traumatic event (< 1 month) and willing to participate in the study. The trauma will be defined as a direct exposure, directly witnessing trauma to a third party, or discovering that a traumatic event has happened to a close family member or a close friend. In case of actual death or death threat to a member of the family or a friend, the event(s) must have been violent or accidental. We will also consider the recurrent or extreme occupational exposure to traumatic events (e.g. front-line workers collecting human remains, police repeatedly exposed to explicit child sexual abuse) [4]. Furthermore, participants must be affiliated to the French public health insurance system, and provide written informed consent. In case of an adult under curatorship, the recruiter will seek only his/her consent, the consent of the curator being not mandatory in the French law.

Patients who are either unable to communicate fluently in French or under guardianship, and/or have clinical instability that makes completing the questionnaire(s) impossible (e.g. agitation, critical condition, distorted consciousness, etc.) will not be included in the study.

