#### PTSD risk factors

Table 2 summarizes the biopsychosocial factors that have the potential to increase PTSD occurrence. These factors will be assessed at inclusion in the ED. Estimated time for documenting all the questionnaires is around 30 min.

**Table 2 Tab2:** PTSD risk factors evaluated in the study, evaluation instruments and timing

Factor Category	Predictive Factors	Measure	Timeline
Trauma Characteristics	Type and timing of the trauma	Pre-screening questionnaire	1st visit
	After trauma: Hospitalization (±); Intensive care (±)	Consumer file	1st visit
Demographics	Sex	Consumer file	1st visit
	Age	Consumer file	1st visit
	Socio-economic status	Self-administered questionnaire	1st visit
	Educational level	Self-administered questionnaire	1st visit
	Marital status	Self-administered questionnaire	1st visit
Biological	Heart rate	Consumer file	1st visit
	Blood pressure	Consumer file	1st visit
	Blood alcohol level	Consumer file	1st visit
Psychological	Trauma history	Self-administered questionnaire	1st visit
	Chronic anxiety	STAI-Y (A & B forms) [68, 69]	1st & Final visits
	Past and current psychiatric pathology	Self-administered questionnaire	1st visit
	Current psychotropic treatment at inclusion and during the 3-month period	Self-administered questionnaire	1st & Final visits
	Psychological care during the 3 months	Self-administered questionnaire	Final visit
	Dissociative Experiences	Self-administered questionnaire: PDEQ [70]	1st visit
Social	Alcohol misuse	Self-report: AUDIT [73, 75]	1st & Final visits
	Smoking addiction	Self-administered questionnaire: Fagerström test [74]	1st & Final visits
	Family history of psychopathy or instability	Self-administered questionnaire	1st visit
	Marital stability	Self-administered questionnaire	1st visit
	Social support	Self-administered questionnaire: SSQ6 [71, 72]	1st & Final visits
Others	Somatic pathology	Patient file	1st visit
	Emergency care time	Patient file	1st visit

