### Sample size

The total number of ED visits in the assigned six centers over a period of 1 month is more than 20,000. We plan to screen around 15,000 patients (75%) with an age range of 18 to 70. Following a traumatic context, 10 to 50% of survivors consult EDs [3, 15, 79, 80]. Considering the most conservative hypothesis (10% of the 15,000 visiting 18–70 year old patients), we estimate that 1500 patients could be included in the study to participate in the cross-sectional part of the study.

The main objective of the cohort study is to identify factors associated with the occurrence of 3-month PTSD. In the literature, incidence of PTSD in various populations and after different types of trauma usually ranges from 30 to 60% [3, 15, 79, 80]. Considering the hypothesis of a 40% incidence of PTSD in the “unexposed” group, the inclusion of 305 patients should allow, with an alpha risk of 0.05, and a power of 80%, to identify factors associated with a relative risk of at least 1.4 [81].

As we anticipate 30% of the subjects may be either lost to follow-up or unwilling to participate at 3 months, we will randomly select a cohort of 400 patients.

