#### Secondary outcome criteria analysis

In the cross-sectional study subjects, we will analyze the proportion of patients at moderate risk (IES-R score 12 to 34) and at high risk (IES-R score > 34) of PTSD at inclusion and their 95% confidence interval.

In the cohort study population, we will analyze the proportion of subjects with a diagnosis of PTSD at 3 months with its 95% confidence interval.

To describe results of the questionnaires, we will consider total score of PDEQ, STAI-Y (A & B forms), AUDIT, Fagerström, QIDS-SR16 and SSQ6 evaluated at inclusion. To present the results of the questionnaires at 3 months, we will focus on total score of STAI-Y (A & B forms), AUDIT, Fagerström, QIDS-SR16 and SSQ6 evaluated again after 3 months.

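### The cohort's 3-month PTSD "incidence" is estimated as a prevalence: PTSD already present before the index trauma is not separated, which modestly overstates incidence and partly inflates psychiatric-history predictors

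*Protocol article*

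**What the plan says.** The cohort's primary objective is to find predictors of PTSD occurring by 3 months. The secondary objective adds that "At 3 months, the incidence of PTSD, its complications and comorbidities will be estimated". The Sample size section uses the same term: "Considering the hypothesis of a 40% incidence of PTSD". The Primary outcome criteria analysis carries it on, expecting 122 PTSD cases among 305 analysable patients.

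The measurement and analysis are as follows:

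- **Measurement.** Table 1 places the PCL-5 at the 3-month telephone interview only. The IES-R at inclusion asks about the last 7 days.
- **Eligibility.** The exclusions are inability to communicate in French, guardianship and clinical instability. Existing PTSD is not among them.
- **Estimator.** Under Secondary outcome criteria analysis, for the cohort population, "we will analyze the proportion of subjects with a diagnosis of PTSD at 3 months with its 95% confidence interval".
- **Predictors.** Table 2 lists "Past and current psychiatric pathology", trauma history and current psychotropic treatment, self-reported at the first visit. They appear as candidate risk factors; nothing says they define who was free of PTSD beforehand.

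**The concern.** Incidence needs a population free of the condition at the start. Here nobody is identified as already having PTSD, so the estimator gives the proportion who have it at 3 months, whenever it began. The IES-R cannot fill the gap: its 7-day window describes current symptoms and does not date them relative to a trauma up to a month old.

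Two results are affected. The incidence estimate takes in old cases. More importantly for the primary objective, the predictors that mark earlier illness (psychiatric history, current psychotropic treatment) are associated with the outcome partly because they identify patients who already had it. A variable that includes current psychiatric pathology can contain the outcome itself. The Discussion wants the results to guide preventive screening, which requires telling patients who will develop PTSD from those who arrive with it.

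**Working it through.** **The plan's own figure.** The Sample size section states that "the inclusion of 305 patients should allow", "with an alpha risk of 0.05, and a power of 80" per cent, "to identify factors associated with a relative risk of at least 1.4". I assume a two-sided test and equal groups, as neither is stated. The risks are 0.40 and 0.40 × 1.4 = 0.56, with mean 0.48.

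n per group = [1.96 × √(2 × 0.48 × 0.52) + 0.8416 × √(0.40 × 0.60 + 0.56 × 0.44)]² / 0.16² = (1.385 + 0.587)² / 0.0256 ≈ 152

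The total is 304 against 305 stated, and power at 305 is 80.2%. Also 305 × 0.40 = 122. The sample size reproduces; the point concerns what the 40% measures.

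**Inputs for the bias.**
- From the article: mean PTSD duration 5.3 years, lifetime PTSD prevalence 3.9%, lifetime trauma exposure 72.7% (all Background); 305 patients and 122 cases.
- Assumed: π, the share with PTSD before the index trauma, 2% to 4%; q, the share of those positive at 3 months, either 0.80 or exp(−0.25/5.3) = 0.954 (exponential duration); h, the share of the cohort with the history factor.

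**Incidence, true risk I = 40%, q = 0.954.** Apparent proportion = πq + (1 − π)I.
- π = 2%: 0.0191 + 0.3920 = 41.1%, excess 1.1 points.
- π = 3.9%: 0.0372 + 0.3844 = 42.2%, excess 2.2 points. Old cases are 0.0372/0.4216 = 9% of those counted.

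**Incidence, working back from 122 observed cases, q = 0.80.**
- π = 2%: 305 × 0.02 × 0.8 = 4.9 old cases; (122 − 4.9)/298.9 = 39.2%, excess 0.8 points.
- π = 4%: 305 × 0.04 × 0.8 = 9.8 old cases; (122 − 9.8)/292.8 = 38.3%, excess 1.7 points.

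For comparison, the 95% confidence half-width for 40% of 305 is 1.96 × √(0.24/305) = 5.5 points.

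**Predictors.** Suppose the factor contains all prior cases and has no true effect on new PTSD.

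| Factor | π, q | Risk with factor | Risk without | Crude OR |
|---|---|---|---|---|
| h = 30% | 4%, 0.80 | (9.76 + 79.3 × 0.383)/91.5 = 43.9% | 38.3% | 1.26 |
| h = 30% | 3.9%, 0.954 | 0.13 × 0.954 + 0.87 × 0.40 = 47.2% | 40% | 1.34 |
| h = 72.7% | 4%, 0.80 | (9.76 + 209.5 × 0.383)/221.7 = 40.6% | 38.3% | 1.10 |

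In the second row, a factor with no true effect would reach 5% significance in about 22% of studies of 305 patients. The third row represents a yes/no trauma history at the article's lifetime exposure figure.

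**Cost of separating prior cases.** At π = 3.9%, 305 × 0.961 = 293 remain, and power for 40% against 56% is 78.6%.

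**The case against.** The endpoint is the presence or absence of PTSD at 3 months, and for emergency-department screening it is legitimate to ask who has PTSD then, whenever it began. That stands, and is why the all-patient model should be kept. It does not justify calling the result incidence.

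The PCL-5 may be anchored to the index trauma. The interviewers are specially trained mental health professionals, the interview is timed from that trauma, and an article commonly leaves such instructions to the full protocol. Its absence here is therefore not a fault, and anchoring would shrink the bias. It might not fully separate overlapping symptoms.

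Three stronger readings are tempting and go beyond the document:

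- **That the bias matches the effect the study is designed to detect.** With 10% prior PTSD and q = 0.80, the 30% factor would show a relative risk of 50.4/35.6 = 1.42. But 10% has no source in the article. Even 3.9% is a lifetime figure that includes remitted cases, so current prevalence in that population would be lower. Emergency trauma patients may carry more prior PTSD, but no figure is given.
- **That the associations are false.** The Background already lists prior traumatic exposure and pre-existing mental health problems as known predictors. A null factor only isolates the size of the bias; real associations would be partly inflated.
- **That recurrent occupational exposure brings in many existing cases.** The eligibility text says "We will also consider the recurrent or extreme occupational exposure to traumatic events", but as one part of the trauma definition within a required recent event. Nothing in it indicates how many such patients already have PTSD.

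**Conclusion.** The point holds in moderate form. The plan calls a 3-month prevalence incidence and, as written, lets PTSD older than the index trauma count as an outcome. The incidence excess is about 1 to 2 points at 2% to 4% prior PTSD and a 40% risk, inside the sampling error. The effect on predictors matters more: a crude odds ratio of about 1.26 to 1.34 for a 30% factor without true effect at about 4% prior PTSD. That is an upper case for this prevalence and factor share, because it assumes every prior case carries the factor. Trauma history as a common yes/no variable is affected much less, about 1.10.

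The mislabelling and the direction of the bias, absent anchoring, follow from the document. The size rests on assumed values for prior prevalence, persistence and factor share. The sample size of 305 is not put in doubt by this point.

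**What to change.** 1. Label the all-patient figure as the prevalence (proportion) of PTSD at 3 months.
2. Use the inclusion self-report of past and current psychiatric pathology to flag PTSD present before the index trauma, with PTSD as a named option if it is not one already.
3. Report incidence in patients without the flag.
4. Pre-specify a repeat of the predictor model in those patients, presented alongside the all-patient model. Restricting the primary model itself would change its target population and is not needed.
5. If the full protocol ties PCL-5 answers to the index trauma, say so.

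The cost is wording, at most one added questionnaire option, and one further model. The restricted analysis loses a few per cent of patients: about 293 of 305 at 3.9%, with power of about 78.6% instead of 80.2%. The flag relies on self-report and will miss undiagnosed prior PTSD, so it reduces the bias without removing it.
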